#### Effect evaluation

Descriptive statistics will be used to describe the study groups regarding their sociodemographic characteristics and baseline scores of the primary and secondary outcomes. The primary and secondary outcomes will be analysed according to the intention to treat principle, that is, all available data from all participants will be included in the analysis. Mixed (multilevel) linear regression will be applied with repeated outcome measures (baseline, post-test) nested in clients nested in nursing teams. ‘Nursing team’ is treated as random effect and outcome predictors are: intervention (yes/ no), time (baseline/ post-test), the intervention by time interaction, working area and its interaction with time, as well as the following covariates and their interactions with treatment and time: 1) older adults’ initial level of disability (measured by means of the GARS [50]); 2) client type (existing vs. new clients); 3) working areas. The design, with one team per working area per treatment condition, does not allow including a random team effect and working area by treatment interaction at the same time, because the team effect is completely confounded with the latter interaction. Team is here the unit of randomisation and therefore treated as random. However, to explore interaction of treatment with working area, an additional analysis will replace the random team effect with that interaction and three-way interaction area*treatment*time. If interaction is found, the treatment effect will be evaluated per working area. The software package SPSS for Windows, version 24.0., will be used for all statistical analyses. The level of statistical significance will be set at 0.05 (using two-tailed tests). If interaction effects for the three covariates (i.e. older adults’ initial level of disability; client type; and working area) are present subgroup analyses will be conducted with a significance level of 0.10. The subgroup analyses will have an exploratory purpose only in view of the risk of type I errors due to multiple testing and of type II errors due to reduced sample size.

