#### Primary outcome measure

The aim of the ‘Stay Active at Home’ programme is to reduce sedentary behaviour in older adults and thereby increase their level of physical activity. The primary outcome sedentary behaviour at 12 months will be measured by means of a tri-axial wrist-worn accelerometer (ActiGraph GT9X Link, ActiGraph Inc., Pensacola, FL, USA). Accelerometers are a valid and reliable method, also in older adults, to measure sedentary time and physical activity by assessing the magnitude of the body’s acceleration in terms of ‘counts’ per unit time [39–43]. The ActiGraph will be placed on the non-dominant wrist and will be worn for seven consecutive days (24 h per day) at baseline and 12 months after baseline. As the accelerometer will also be worn during the night, information about sleep will also be obtained. Older adults are asked to keep a diary to register when they went to bed, when they got up and when they were napping during the day. Data will be collected at 30 Hz and will be aggregated to 60-s epochs for the analyses [44]. Older adults are required to have at least 1 valid day of 10 h of wake wear time to be included in the analyses. In additional analyses, older adults with four or more valid days will be selected. Waking time and wear time will be defined by an algorithm available in the ActiLife software version 6. Activity counts will be converted into average daily minutes of sedentary behaviour during waking time using a vector magnitude cut-point of < 1853 cpm [45]. In addition, mean wake time activity counts per minute will be compared between groups (secondary outcome).

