### Sample size

The sample size calculation will be based on the primary outcome of this study, namely sedentary time as measured by the ActiGraph GT9X Link (ActiGraph Inc., Pensacola, FL, USA). The ‘Stay Active at Home’ programme is expected to create a 15% difference in sedentary time (minutes/ day) between the groups. Based on a mean of 535.9 min (*SD* = 145.7) [45] this is equivalent to an effect size of 0.55, which can be interpreted as a medium effect size according to Cohen [63]. To achieve a power of 80% with an alpha of 0.05 (using two-tailed tests) requires a minimum sample size of 54 clients per group *(N =* 108 in total). Considering an expected drop-out rate of 30% before post-test, a total sample size of 154 older adults is needed. Finally, to compensate for a) the inflation of sampling error arising from a clustering effect and b) a mild variation in sample size per nursing team, a correction will be applied, taking into account an intraclass correlation of 0.02 and a coefficient of variation of 0.50, resulting in a total sample size of 260 older adults (130 for each arm) [64].

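### The effect on 12-month sedentary time is estimated as a difference in change without adjusting for its own baseline, which loses precision; the same model breaks down when GARS is the outcome

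*Protocol article*

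**What the plan says.** The section on the primary outcome measure fixes the endpoint at one time point: "The primary outcome sedentary behaviour at 12 months will be measured" by accelerometer, with the same measurement at baseline.

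The effect evaluation under Data analyses specifies a mixed linear regression with baseline and post-test nested in clients and clients nested in teams. Team is random, and "outcome predictors are: intervention (yes/ no), time (baseline/ post-test), the intervention by time interaction". The listed covariates are initial GARS, client type and working area, each interacting with treatment and time. Baseline sedentary time appears only as an outcome row. The same specification is applied to the primary and the secondary outcomes, and GARS is one of the secondary outcomes in Table 1.

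The Sample size section plans on a plain two-group comparison: the programme is "expected to create a 15% difference in sedentary time (minutes/ day) between the groups". With a single-measurement SD, "145.7) [45] this is equivalent to an effect size of 0.55". It states neither an SD of change nor a baseline-to-follow-up correlation.

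**The concern.** With a free intervention main effect, the intervention-by-time term is the between-arm difference in change from baseline. For one client, with correlation r between baseline and follow-up, a change score has variance 2(1−r)σ². The follow-up value regressed on baseline has residual variance (1−r²)σ². The second is smaller at every r below 1, so the planned model gives up precision on the primary outcome although the baseline value is there to be used. The sample size was built on σ² itself, which a change score matches only at r = 0.5.

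The GARS problem is of another kind. If initial GARS and its interactions are predictors, the baseline row of the GARS outcome is predicted by itself without error. What is at stake there is the validity of a standard error, not efficiency.

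**Working it through.** **The plan's own figure.** 15% of 535.9 is 80.4 min; 80.4/145.7 = 0.552, as stated. A two-sided t-test at 0.05 with 54 per arm has 81% power, so "To achieve a power of 80% with an alpha of 0.05 (using two-tailed tests) requires a minimum sample size of 54 clients per group" reproduces to within a client or two. 108/0.7 = 154.3, which gives 154. The final 260 is taken as stated.

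**Individual level, 54 per arm, d = 0.55, complete cases** (r assumed):

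| r | 2(1−r) | 1−r² | power, change | power, adjusted |
|---|---|---|---|---|
| 0.3 | 1.40 | 0.91 | 67% | 84% |
| 0.4 | 1.20 | 0.84 | 73% | 87% |
| 0.5 | 1.00 | 0.75 | 81% | 91% |
| 0.6 | 0.80 | 0.64 | 89% | 94% |

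Against the planning figure, a complete-case change score is below 80% when r is under about 0.5.

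**The trial as sized.** This table leaves out two features of the plan: clients with baseline only stay in the model, and teams are random. Take σ² = 1, intraclass correlation 0.02, 5 teams per arm of 26 clients (equal sizes assumed), and 0.7 × 26 = 18.2 clients per team with 12-month data. Let b be the within-team slope of follow-up on baseline. Keeping baseline-only clients makes the client-level factor for change, per completer, (1−b²) + 0.7(1−b)².

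Team effect constant over time, b = (r−0.02)/0.98:
- V(change) = (2/5) × 0.98[(1−b²) + 0.7(1−b)²]/18.2
- V(adjusted) = (2/5) × {0.02(1−b)² + 0.98(1−b²)/18.2}

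Team effects independent over time, b = r/0.98:
- V(change) = (2/5) × {0.04 + 0.98[(1−b²) + 0.7(1−b)²]/18.2}
- V(adjusted) = (2/5) × {0.02(1+b²) + 0.98(1−b²)/18.2}

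Example, constant team effect, r = 0.3: b = 0.286, 1−b² = 0.918, (1−b)² = 0.510. V(change) = 0.4 × 0.98 × 1.275/18.2 = 0.0275. V(adjusted) = 0.4 × (0.0102 + 0.0495) = 0.0239. Ratio 0.87.

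Power uses Φ(0.552/√V − 1.96):

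| r | ratio adjusted/change, constant | power, change | ratio, independent | power, change |
|---|---|---|---|---|
| 0.2 | 0.85 | 88% | 0.63 | 73% |
| 0.3 | 0.87 | 91% | 0.66 | 76% |
| 0.4 | 0.89 | 95% | 0.70 | 79–80% |
| 0.5 | 0.91 | 97% | 0.73 | 83% |
| 0.7 | 0.95 | over 99% | 0.81 | 91% |

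These are normal-approximation figures that ignore the few cluster degrees of freedom. The plan expects unequal teams (coefficient of variation 0.50), which lowers power somewhat.

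**GARS as outcome.** Let n clients per arm have a baseline and 0.7n a follow-up, with follow-up residual variance s² given baseline. Baseline rows have residual zero, so a common residual variance is estimated as 0.7s²/1.7 = 0.412s². The model then reports a variance for intervention by time of 0.412s² × 2(1/n + 1/0.7n) = 1.00 × 2s²/n. The true variance is 2s²/(0.7n) = 1.43 × 2s²/n. The standard error is too small by the factor √0.7 = 0.837, or 16%, and the type I error is 2Φ(−1.96 × 0.837) = 10%. An individual-level simulation with 30% drop-out gave about 18% and a type I error near 11%. With no drop-out the two errors cancel.

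**The case against.** The strongest defence is that a free baseline difference is deliberate. District nurses screen clients on clinical judgement, clients follow their team's allocation, and the Design section gives the arms different recruitment windows. Baseline differences may therefore be real, and adjusting for an error-prone baseline (one valid day suffices) can leave residual bias. That point is fair, though the article does not offer it as a reason. It justifies keeping the change model in view, not ignoring baseline sedentary time in the primary analysis.

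It is also fair that the present model uses every client with any measurement, that a team effect constant over time drops out of the change, and that GARS, client type and area are already adjusted for. The first two points shrink the gain well below the individual-level figure: the ratio at r = 0.4 is 0.89 with a constant team effect, not (1+0.4)/2 = 0.70.

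A reader might infer from the 54-per-arm table that the trial falls under 80% power whenever r is below 0.5. The document does not support that. It enrols 260. With the single random team effect it describes, power for the change estimate is about 88% even at r = 0.2; it drops below 80% near r = 0.4 only if team effects are uncorrelated over time. No r is stated. Nor is it right to call the analysis unadjusted: only the outcome's own baseline is missing from the covariates.

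No part of this defence answers the GARS problem.

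**Conclusion.** The concern holds as one of avoidable imprecision. At r from 0.3 to 0.7, baseline adjustment lowers the variance of the primary effect by about 5 to 13% if team effects are constant over time and about 19 to 34% if they are independent; it was the more precise analysis at every r tried. This rests on assumed r, an intraclass correlation of 0.02, 30% drop-out and equal teams. No general power shortfall should be claimed. Only the individual-level planning figure is undercut when r is below about 0.5, and then for a complete-case change score.

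The GARS specification is a defect whatever r is: the baseline row is fitted exactly, and with drop-out and a common residual variance the test is too liberal, with a type I error of roughly 10 to 11% instead of 5%.

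**What to change.** Make the primary model a mixed regression of 12-month sedentary minutes on intervention, the client's baseline sedentary minutes, working area, baseline GARS and client type, with a random nursing-team intercept. Use the same form for each continuous secondary outcome with its own baseline. For GARS, baseline GARS enters once, as a covariate only. Keep the current repeated-measures model as a pre-specified sensitivity analysis for all outcomes except GARS, because recruitment is arm-specific and real baseline differences are possible.

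The change is to analysis wording and needs no new data. It has three costs. Clients without a valid baseline need a simple stated rule, such as mean imputation of the baseline. Clients with baseline only no longer contribute to the primary model. And if there is true baseline imbalance the two models may disagree, which is why both should be reported.

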The Groningen Activity Restriction Scale (GARS, [50]) will be used to collect data about daily functioning. The GARS consists of two subscales and assesses disability in the domains of activities of daily living (ADL, 11 items, such as dressing or getting around in the house) and instrumental activities of daily living (IADL, 7 items, such as preparing breakfast or doing household activities) [50]. For each item, four hierarchical answer options are available ranging from *‘Yes, I can do it fully independently without any difficulty’* to *‘No, I cannot do it fully independently. I can only do it with someone’s help’*. The scores for the total scale range from 18 to 72 with higher scores indicating more disability [50]. The GARS is a reliable and valid measure for assessing disability in the domains of ADL and IADL in older adults [50].

The Patient Health Questionnaire-9 (PHQ-9, [47]) will be used to assess psychological functioning. The PHQ-9 consists of nine items which measure the presence of depressive symptoms according to the Diagnostic and Statistical Manual of Mental Disorders, 4th Edition (DSM-IV). Older adults will score how often each of the symptoms (such as ‘little interest or pleasure in doing things’ or ‘feeling tired or having little energy’) was present during the last two weeks (0 = not at all; 1 = several days; 2 = more than half of the days; 3 = nearly every day). The summary score ranges from 0 to 27, with higher scores reflecting more severe symptoms of depression. The PHQ-9 has been shown to be a valid and reliable instrument to measure depression in community-dwelling older adults [51].

Finally, the frequency of falls will be assessed by the question: *‘How often did you fall during the past 6 months’* [52]. This question is included to monitor a potential negative outcome of physical activity, despite research showed that stimulating older adults to be more active does not necessarily lead to an increase in fall incidents [53].

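### The primary model's covariate list includes an area-by-treatment term that the protocol itself says cannot sit beside the random team effect; the primary contrast is left undefined, and the additional per-area analysis tests team variation as effect modification

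*Protocol article*

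**What the plan says.** All of this is in the protocol article, Data analyses, Effect evaluation, unless stated otherwise.

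- Random part and first predictors: "Nursing team’ is treated as random effect and outcome predictors are: intervention (yes/ no), time (baseline/ post-test").
- Next predictors: "the intervention by time interaction, working area and its interaction with time".
- Then a covariate list, introduced by "as well as the following covariates and their interactions with treatment and time". Item 1 is initial disability on the GARS; the list goes on with "2) client type (existing vs. new clients); 3) working areas".
- The sentence after the list says the design "does not allow including a random team effect and working area by treatment interaction at the same time", because with one team per area and arm the two are aliased.
- The choice between them: "Team is here the unit of randomisation and therefore treated as random". Area-by-treatment and area-by-treatment-by-time go to an additional analysis in which they take the place of the random team effect. After that: "If interaction is found, the treatment effect will be evaluated per working area".
- On the GARS, under Secondary outcome measures: "The scores for the total scale range from 18 to 72".
- Interactions with any of the three covariates lead to subgroup analyses at the 0.10 level, labelled exploratory because of multiple testing and smaller samples.

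**The concern.** Three things in this paragraph do not fit together.

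1. **The list contradicts the next sentence.** Working area and area-by-time are already in the model before the covariate list begins. The only thing item 3 can add is area's interaction with treatment, which is exactly the term then ruled out.
2. **The primary contrast is not fixed.** Moving area-by-treatment elsewhere leaves the treatment interactions of GARS and client type in the primary model. With those present, the intervention-by-time coefficient is the effect at the zero point of each covariate, wherever the coding puts it. The paragraph does not say whether the primary result is that coefficient, an average effect, or an effect from a model without the interactions.
3. **The additional analysis omits team variance.** Once random team is removed, each area's effect is one team against one team, judged against client-level error only. Ordinary differences between two teams then count as evidence that the programme works differently by area.

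At stake are which number is the primary result, a choice that should not be open once data are seen, and whether area-specific claims could rest on team noise.

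**Working it through.** The protocol states no figure on this point, so there is none to reproduce first.

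**1. Can the listed model be fitted?** Inputs: ten teams, five areas, one team per area and arm (Randomisation; Effect evaluation). Count team-level fixed parameters:
- intercept 1 + treatment 1 + area 4 = 6, leaving 10 − 6 = 4 df for team;
- adding area-by-treatment (4 more) = 10, leaving 10 − 10 = 0 df for team.

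A numerical rank check of the design matrix gives the same 6 and 10. The count also applies to change from baseline, where area-by-treatment-by-time takes the same 4 df. With the term in, team variance cannot be estimated; without it, the model can be fitted.

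**2. What does the intervention-by-time coefficient estimate?** With three-way terms for GARS (g) and client type (c), the effect on change is

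effect(g, c) = β + γ·g + δ·c,

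so β is the effect at g = 0 and c = 0. If GARS is uncentred, g = 0 lies below the scale minimum of 18. One simulated data set illustrates this. Assumptions: 26 clients in each of 10 teams, GARS mean 35 and SD 9, 30% in one client type, average effect −40 min, team SD 20 and residual SD 140 on change.

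| Model (random team, area main effects) | Treatment coefficient | SE |
|---|---|---|
| No treatment-by-covariate terms | −47.8 | 17.6 |
| Interactions, covariates centred | −47.8 | 18.0 |
| Interactions, GARS uncentred, client type 0/1 | −101.0 | 71.5 |

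The first two rows agree; the third answers a different question. If only two-way terms are meant, covariate-by-treatment is averaged over baseline and follow-up and does not test modification of change.

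**3. The area-by-treatment-by-time test without random team.** Inputs from Sample size: ICC 0.02, 260 clients, 30% drop-out, so 260 × 0.7 / 10 = 18.2, taken as 18 analysed clients per team. Assumed: team autocorrelation r_t of 0.5–0.8 and client correlation r_c of 0.5–0.7 between baseline and 12 months.

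On the change scale, team variance is 2 × 0.02 × (1 − r_t) and client variance is 2 × 0.98 × (1 − r_c). With no true interaction, the F ratio is inflated by

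λ = 1 + 18 × 0.02 × (1 − r_t) / [0.98 × (1 − r_c)].

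The 5% critical value of F on 4 and 170 df is 2.42, and the true rejection rate is P(F > 2.42/λ):

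| r_t | r_c | λ | Rejection rate |
|---|---|---|---|
| 0.8 | 0.5 | 1.15 | 8.1% |
| 0.8 | 0.7 | 1.24 | 10.5% |
| 0.5 | 0.5 | 1.37 | 13.6% |
| 0.5 | 0.7 | 1.61 | 20.3% |

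The table assumes equal team sizes. Simulation with the protocol's coefficient of variation of 0.50 lowers the rates a little, to about 8–19% overall. If team effects were perfectly stable over the year (r_t = 1), λ = 1 and the rate is 5%, so the excess comes from team-level change.

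**4. The per-area step.** It runs only if the interaction is found, so its false-positive rate cannot exceed that of the gate. In simulation it is about the same as the gate's, because a significant interaction nearly always comes with at least one significant pair.

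**The case against.** The strongest reply is that the paragraph repairs itself: it explains the aliasing, keeps team random and sends area-by-treatment elsewhere, so only one primary model that can be fitted survives. This stands as a reading of intent. It does not make the list correct, and it does nothing about the GARS and client-type interactions.

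Second, centring and contrast coding are details that an article may leave to the analysis plan. That is fair, and it rules out some stronger readings. A reader might infer that the model yields no overall treatment effect; it does, through centring, sum coding or marginal means. A reader might also infer that power collapses, because the SE at GARS = 0 is √(1 + (mean/SD)²) times the SE at the mean, or 2.7–5.1 times for an assumed mean of 30–40 and SD of 8–12. That needs uncentred GARS and moments the protocol does not give, so it shows what one coding error would cost and says nothing about the stated plan. What remains is that the paragraph writes the model out and does not say which contrast is primary.

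Third, the area analysis is disclosed as exploratory and the aliasing is admitted. That limits the harm, since no primary conclusion rests on it. But the stated reasons for caution are multiplicity and small subgroups; omitted team variance is a separate fault that they do not cover. A reader might quote the 28–45% chance that at least one of five ungated team pairs is significant. That overstates the problem: five valid tests already give 1 − 0.95⁵ = 22.6%, and the plan gates the step on an interaction.

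**Conclusion.** The concern holds in limited form.

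- **Certain, free of assumptions:** the covariate list contradicts the sentence after it. The listed model leaves 0 df for team; the evidently intended one leaves 4. It would be wrong to conclude that the primary analysis cannot be done.
- **Follows from the text:** with GARS and client type interacting with treatment, the intervention-by-time coefficient depends on coding, and the primary contrast is not named. The average effect is recoverable.
- **Conditional in size:** the additional analysis treats team variation as effect modification. At the protocol's ICC of 0.02 the interaction test rejects in about 8–19% of trials with no true interaction, instead of 5%, and the gated per-area procedure has about the same rate. This rests on the assumed team autocorrelation (0.5–0.8) and client correlation (0.5–0.7), with 18 analysed clients per team and testing at 0.05.

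**What to change.** 1. Delete item 3, working areas, from the covariates that interact with treatment in the primary model. Area and area-by-time are already there.
2. Take the primary intervention-by-time test from a model with random team, intervention, time, intervention-by-time, area, area-by-time, and baseline GARS and client type with their time interactions only. Alternatively, keep the treatment interactions, centre the covariates and name the average effect as primary.
3. Test GARS-by-treatment-by-time and client-type-by-treatment-by-time in separate exploratory models, written as three-way terms.
4. Replace the per-area tests with a descriptive display of the five within-area differences, stating that area-by-treatment and team effects cannot be separated in this design.

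The cost is wording in the protocol or analysis plan; no data collection changes. The downside is that significance claims for single areas are given up.

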### Randomisation

For this study, ten nursing teams in five working areas (two teams per area) will be selected by the nursing team managers of MeanderGroep. To avoid contamination bias, managers will be asked to select two teams within each area that are not collaborating with each other. Furthermore, dementia teams will not be considered, as most of their clients potentially will not fulfil the inclusion criteria for older adults. The nursing teams will be pre-stratified with regard to their working area and randomised into either the intervention or control group within each working area. The clients and, if applicable, their DSWs will be allocated to the intervention or control group based on the allocation of the nursing team. The randomisation will be conducted by means of a computer-generated randomisation list. The researcher who will conduct the randomisation, will be blinded, will not be involved in this study and not familiar with the nursing teams. A flow diagram of the study design is shown in Fig. 1.

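### The working-area interaction analysis drops the random team effect and then acts on the result, although with one team per arm per area a rejection cannot be told apart from ordinary team differences

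*Protocol article*

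**What the plan says.** Under Randomisation, the protocol article selects "ten nursing teams in five working areas (two teams per area"), and these are "randomised into either the intervention or control group within each working area". Each area therefore contributes exactly one intervention team and one control team.

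Under Data analyses, Effect evaluation, the main model treats nursing team as random because it is the unit of randomisation. The article explains that a random team effect and an area-by-treatment interaction cannot be fitted together, "because the team effect is completely confounded with the latter interaction". To explore that interaction nonetheless, "an additional analysis will replace the random team effect with that interaction and three-way interaction area*treatment*time". The rule attached to it is: "If interaction is found, the treatment effect will be evaluated per working area".

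Working area is also one of three covariates for which, if interactions "are present subgroup analyses will be conducted with a significance level of 0.10". The same section adds: "The subgroup analyses will have an exploratory purpose only", giving multiple testing and reduced sample size as the reasons.

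Under Sample size, the calculation allows for clustering, "taking into account an intraclass correlation of 0.02 and a coefficient of variation of 0.50".

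**The concern.** The question asked is whether the programme works differently in different areas. In this design, the four degrees of freedom for area-by-treatment are the between-team variation that remains after area and treatment are accounted for. Removing the random team effect does not break that identity. It only changes the yardstick from between-team to between-client variation, so the test behaves as if teams did not differ, while the sample size section assumes that they do.

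A rejection may then mean no more than that teams differ, yet the plan responds with area-specific treatment effects. Each of these compares one team with one team, with no between-team degrees of freedom. A reader could take such results as evidence that the programme works in some areas and not in others, which this design cannot show.

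There is also a contradiction within the section. It lists working area among the covariates whose interactions with treatment and time enter the random-team model, and the next sentence says the area-by-treatment interaction cannot be included there.

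**Working it through.** **Inputs from the protocol article.** 10 teams, 5 areas, one team per arm per area (Randomisation). Total sample 260, drop-out 30%, intraclass correlation (ICC) 0.02, coefficient of variation of team size 0.50, SD 145.7 min (Sample size). General significance level 0.05 two-sided, subgroup level 0.10 (Effect evaluation).

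**Clients per team.** 260/10 = 26 enrolled; 26 × 0.7 = 18.2 followed.

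The plan gives no error rate for this test, so there is none to reproduce. A usual cluster correction of the plan's 154 clients gives 154 × [1 + (1.25 × 26 − 1) × 0.02] = 154 × 1.63 = 251, somewhat below the stated 260. The point does not rest on that gap.

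**Area-by-treatment, no team term.** With the same effect in every area and n clients per team, the F statistic on 4 and 10n − 10 degrees of freedom is inflated by L = 1 + n × ICC/(1 − ICC). The true size is P(F > critical value/L).

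- n = 18.2, ICC 0.02: L = 1 + 18.2 × 0.02/0.98 = 1.37; 2.424/1.37 = 1.77; size 13.8%.
- n = 26, ICC 0.02: L = 1 + 26 × 0.02/0.98 = 1.53; 2.408/1.53 = 1.57; size 18.2%.
- Over ICC 0.01 to 0.05: 9% to 30% at 18.2 per team, 11% to 40% at 26 per team.

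A simulation of the baseline and post-test model agrees. It used 6,000 trials per setting, unequal team sizes, a common effect of 0.15 × 535.9 = 80.4 min in every area, stable team differences and an assumed within-client correlation of 0.6. Size was 14.1% with 182 clients and 19.5% with 260.

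**Area-by-treatment-by-time.** This is a test on change from baseline, so stable team differences cancel. In the same simulation its size was 5.2% and 5.0%. If team effects correlate over time at c and client values at r, L = 1 + n × 0.02(1 − c)/[0.98(1 − r)]. The documents give neither c nor r, so these are assumptions. For n = 18.2:

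| c | r = 0.3 | r = 0.5 | r = 0.7 |
|---|---|---|---|
| 1.0 | 5.0% | 5.0% | 5.0% |
| 0.8 | 7.2% | 8.2% | 10.6% |
| 0.5 | 11.0% | 13.8% | 20.5% |

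**Either term decides.** The rule does not exclude this reading. With stable team differences at ICC 0.02, the simulation gives 18.4% (182 clients) and 23.5% (260 clients), against about 10% with no team variance.

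**Per-area step (post-test difference, n = 18.2).** SE with team variance: 145.7 × √[2 × (0.02 + 0.98/18.2)] = 56 min. SE with no team variance: 145.7 × √(2/18.2) = 48 min. A test at 0.10 that ignores team variance has error 2 × P(Z > 1.645/√1.37) = 16%. At 0.05 it is 2 × P(Z > 1.96/√1.37) = 9%.

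**The case against.** The best defence is that the programme effect in this model is intervention-by-time, so an effect that varies by area is the three-way term. Stable team differences leave that test at 5%, and the ICC of 0.02 is a sample-size input, not a figure for teams drifting apart over time. This stands for the three-way term. It does not rescue the rule, which never names that term, and it needs perfectly stable team differences over 12 months of a programme delivered through teams. Even a test of correct size cannot separate area from team.

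The second defence is disclosure. The confounding is stated, the analysis is additional and exploratory, and the primary model is untouched. That limits the harm. But the confounding is given only as a reason why two terms cannot be fitted together; it is not carried into the reading of the per-area results. The exploratory label cites multiplicity and small samples, not this problem.

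Three stronger readings are tempting and not supported:

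- That the rule fires at two to three times the nominal rate in general. At 18.2 per team this describes the two-way term at ICC 0.02 (13.8/5 = 2.8). For the three-way term it depends on how stable teams are.
- That the plan carries a 58% chance of a false area finding. Five tests with 16% error each give 1 − 0.84⁵ = 58%, but without clustering five tests at 0.10 already give 1 − 0.9⁵ = 41%, which is multiplicity the plan discloses. The plan also looks at areas only after an interaction is found.
- That a positive interaction is nearly always followed by a significant area because of the missing team effect. That happens with any such gate, including a valid one.

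**Conclusion.** The rule is wrong as written and should be changed before analysis. It treats a rejection as an area difference after the same paragraph has said that the two cannot be told apart. At the plan's ICC of 0.02, the area-by-treatment test at nominal 5% has a true size of about 14% to 18%. This assumes that the ICC applies to the quantity tested and that the followed number per team lies between 18.2 and 26. The area-by-treatment-by-time test ranges from 5% to about 20% at 18.2 per team, over the assumed stability values tabulated. Each per-area test at 0.10 has about 16% error when team variance of this size is ignored.

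A reader might infer that the trial's main result is compromised. It is not: the primary treatment effect comes from the model with the random team effect. The problem is confined to the additional analysis and the per-area results that follow from it.

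**What to change.** 1. Delete the rule that an interaction leads to treatment effects per working area.
2. Remove working area from the covariates that interact with treatment in the random-team model, and from the covariates that trigger subgroup analyses at 0.10. Working area and its interaction with time can stay as stratification terms.
3. Report the five within-area differences in change from baseline descriptively, without area-specific conclusions. State that area and team effects cannot be separated with one team per arm per area.
4. If an interaction test is kept, name area-by-treatment-by-time as the deciding term and state that it is valid only conditional on these ten teams.

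The cost is a change of wording in the analysis section. What is lost is a formal area-interaction test, and area-specific claims, that the design cannot support.
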